**Fig. 1 Fig1:**
[figure not shown]
Mixed-methods study diagram

At the health facility, participants will first undergo baseline assessment of leaking freely (six hours). Participants will be block randomized within a crossover design [61] to varying sequences of leaking freely, using the cup, and using the cup+ (Fig. 2). During clinic-based assessment, the study will quantitatively evaluate short-term comparative efficacy (at six hours) between the cup and the cup + and assess medium-term comparative effectiveness (at 24 h). Participants will be subsequently individually randomized to take home either the cup or the cup + as part of a community assessment of longer-term effectiveness, including change in quality of life (after one to three months). Preliminary clinic- and community-based assessment results will connect the qualitative phase by informing the qualitative stakeholder interview guide and purposive selection of a sub-sample of purposively selected trial participants, partners, and peers (*n* ~ 30). These individuals will be interviewed for an in-depth understanding of user-cup interactions, acceptability, stigma, and quality of life. We will also begin to qualitatively examine the implementation context for the cup and the cup + as perceived by providers (*n* ~ 20).

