#### Quality of life

Using dependent t-test with 2-tailed, alpha error = 0.05, estimated mean difference of effect between the cup and cup + of 40%, and power 0.85 to avoid type 1 error, required sample size is 59. Estimates of the effect are based on data collected within a longitudinal study of post-surgical fistula repair patients in Uganda, [66] wherein participants were asked about quality of life using the post-repair fistula reintegration measure which is standardized to a range of 0-100 [67]. Participants reported a mean of 36.7 (SD = 19.0) at the time of fistula repair (referring to living with fistula) and a mean of 78.0 (SD = 22.7) at follow up (6 months post-repair), reflecting a mean change of 40.5 (SD 28.1): 54.2 (SD 14.5) among those who were not leaking urine and 13.1 (SD 28.9) among those who continued leaking urine. The cup + is estimated to have a comparable improvement on quality of life as surgical repair, while the cup, based on our observations during our feasibility study [37] and on expert opinion, is estimated to have a smaller effect on quality of life over the long-term (3 months) as it has 1/15th of the capacity for urine storage and thus will need more frequent emptying than the cup+.

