##### Data collection

Data will be collected within the clinic-based phase via questionnaire, clinical exam (by a physician), clinical checklist (by nurse/midwife), pad test, and observation (Fig. 1; Table 2). At baseline, a gynecological exam will be carried out as potential participants are being screened and, once enrolled, the baseline questionnaire will be administered. Data will be directly entered into the REDCap mobile app to facilitate data privacy and quality. Next, all participants will be provided disposable pre-weighed adult pads or diapers for the first six hours of each treatment assignment while carrying out typical activities daily living activities on the ward. Six hours was deemed to be a clinically significant amount of time to provide women some relief from their leaking to allow them to engage in social activities or sleep uninterrupted. Additionally, six hours will likely provide those in the cup + assignment the opportunity to fill and then empty their leg bag. Lastly, six hours was deemed logistically feasible for data collectors (i.e., at the start and end of their shift). When assigned to cup or cup+, participants will also insert and wear the respective cups. Women will be encouraged to void ‘normally’ if they sense urgency and instructed to change their diapers as frequently as they see fit when they feel dampness and to deposit the used diapers into a personal plastic Ziplock bag that is then sealed until study staff can record the weight of the wet diapers. At the end of the first six hours of each treatment assignment, the weight of the participant’s assigned dry diapers will be subtracted from that of the wet diapers to calculate the volume of urine leaked, and participants will be asked questions regarding perceived effectiveness. Participants will continue with their assigned treatment until 24 h of use, at which time another questionnaire and a clinical checklist to note any adverse events will be administered by the study physician or nurse/midwife.

**Table 2 Tab2:** Quantitative study measurements, data sources, and timing of assessment

Category	Measure	Data Source^a^	Clinic				Community		
			0h	6h	24h	4d	1m	2m	3m
Outcome variables									
Quality of life ^b,c^	Quality of life (Post-fistula repair reintegration instrument)^*92*^	PS	●				●	●	●
Urine leaked (observed) ^c^	Pad weight; number of pads used, food and fluid intake, voiding	PT, TM		●					

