### Community-based procedures

On the last clinic day, participants will be individually randomized to use of cup or cup + at home for up to three months (see Randomization; Fig. 1) for community-based assessment of the longer-term effectiveness, acceptability of the cup and cup+, and material and opportunity costs to non-surgical fistula management. We will assess perceived change in leakage associated with cup/cup + use, quality of life, acceptability and adherence via survey and clinical checklist administered at one and two months either over the phone as we have done in prior studies [63, 74] or in-person per participant and data collector preference, and semi-structured interview and clinical exam in-person at three months. Participants will be provided with airtime to ensure their ability to contact study personnel.

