##### Quality of life

We will compare mean difference in quality of life score as measured by the post-fistula repair reintegration instrument [83] at 1–3 months compared to baseline using McNemar’s test by intervention and will separately model the trajectory of quality of life across our five assessment points using mixed-effects linear regression analysis of assessment points within individuals. Comparative effectiveness of the cup vs. cup + on quality of life will be assessed by comparing the respective quality of life change using paired t-test. Perceived leakage will be assessed similarly. As we observed a wide variability in baseline leakage in our feasibility study (63.2 ml ± 49.2) [84] and clinical cut points leakage reduction are not established, we will use quality of life estimates to identify a clinically significant leakage reduction. Quantitative measures of *short-term user acceptability* will be described using appropriate distributional statistics and compared between cup vs. cup + using paired t-test (continuous) or McNemar’s test (categorical). Quantitative measures of *long-term acceptability* will be described by cup vs. cup + through modeling their trajectory across community assessment and comparing these statistically using mixed-effects linear regression analysis. In secondary analyses we will assess various potential confounders will for association with the primary outcome variable (% change in volume of urine leaked at 6 h of use) as well as with user acceptability score. A direct relationship will also be assessed between effectiveness (self-perceived change in volume of urine leaked) recorded at 24 h of use and at 1, 2, and 3-month follow-up for both intervention models.

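### The cup versus cup+ quality-of-life comparison is assigned a paired t-test, but each woman takes home only one device, so there are no pairs

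*Protocol article*

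**What the plan says.** - **Analysis.** Protocol article, Data analysis, Quality of life: comparative effectiveness of cup versus cup+ "will be assessed by comparing the respective quality of life change using paired t-test". The next sentence adds: "Perceived leakage will be assessed similarly".
- **Home-phase allocation.** Community-based procedures: "participants will be individually randomized to use of cup or cup + at home for up to three months". Study design says the same, with women "subsequently individually randomized to take home either the cup or the cup"+. The abstract agrees. No switch of device at home is described.
- **Timing.** Table 2 lists "Quality of life (Post-fistula repair reintegration instrument") at 0 h and at 1, 2 and 3 months. It has no entry at 6 h, 24 h or 4 days.
- **Sample size.** Study population and sample size, Quality of life: "Using dependent t-test with 2-tailed, alpha error = 0.05", "estimated mean difference of effect between the cup and cup + of 40"%, power 0.85, giving a required sample of 59.

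**The concern.** A paired t-test works on one difference per woman: her result on cup minus her result on cup+. The home phase never produces that difference. It is a parallel-group trial that follows the clinic crossover, and quality of life is measured only before the crossover and during the home phase.

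This is the randomised comparison behind the second of the two stated sample-size targets. As written, the test either cannot be run or has to be run on women matched arbitrarily across arms, and its standard error and p-value then depend on how the rows are ordered. The instruction on perceived leakage carries the same error into the monthly perceived-leakage data. Because the sample size also assumes pairs, the stated 59 does not describe the comparison that will actually be made.

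**Working it through.** **1. Are there any pairs?**

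| Phase | Devices per woman | Quality of life measured | Cup/cup+ pair within a woman |
|---|---|---|---|
| Clinic crossover (4 days) | both | 0 h only, not tied to a device period | none for quality of life |
| Home (up to 3 months) | one | 1, 2 and 3 months | none |

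The analysis text mentions five quality-of-life assessment points and Table 2 shows four. One more score, wherever it fell, would not give a woman a home-phase change on the second device. Pairing baseline with follow-up in the same woman is a different comparison, and the protocol treats it in a separate sentence.

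**2. Reproducing the stated 59.** Inputs: paired t-test, two-sided alpha 0.05, power 0.85. Reading 40% as a standardised paired effect of 0.40:
- Normal approximation: n = ((1.960 + 1.036)/0.40)² = 56.1, so 57.
- Non-central t: n = 58.07, so 59. Power is 0.850 at n = 58 (0.8496, just short) and 0.856 at n = 59.

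The figure reproduces, and it reproduces as a paired calculation.

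**3. What independent groups need.** The protocol does not say what the 40% is a percentage of. The table uses SD 28.1, the SD of change in the repair cohort that the protocol cites, at two-sided 0.05 and 85% power.

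| Reading of 40% | Points | Effect in SD | Paired n | Independent, per arm |
|---|---|---|---|---|
| Standardised 0.40 | 0.40 × 28.1 = 11.2 | 0.40 | 59 | 114 |
| 40% of the pre-repair mean 36.7 | 14.7 | 0.52 | about 35 | about 67 |
| 40% of the mean change 40.5 | 16.2 | 0.58 | about 29 | about 55 |
| 40 points on the 0–100 scale | 40 | 1.42 | 7 | about 10 |

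Of these readings only the first gives 59. For independent groups it needs 2 × 114 = 228 analysable women, or 228/0.80 = 285 enrolled. That is 228/59 = 3.9 times the stated number.

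**4. What the planned trial delivers.** 100 enrolled × 0.80 retained = 80, or 40 per arm at 1:1 (assumed; the ratio is not given).
- Two-sample t-test, 78 df, 85% power: detectable effect 0.678 SD, and 0.678 × 28.1 = 19 points.
- Adjusting for baseline multiplies the detectable effect by √(1 − r²), in units of the follow-up score's SD. The protocol gives no r. At r = 0.5: 0.678 × 0.866 = 0.59. At r = 0.3 it is 0.65, and at r = 0.7 it is 0.48.
- Power at 0.40 SD, unadjusted: 0.33 with 59 women, 0.42 with 80, 0.51 with 100.

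**5. What arbitrary pairing would do.** With 40 made-up pairs the test has 39 df instead of 78 (critical t 2.023 against 1.991). With equal SDs in the two arms, the paired standard error equals the two-sample one times √(1 − r), where r is the chance correlation created by the ordering. Over random orderings r has SD about 1/√39 = 0.16. One SD either way gives √0.84 = 0.92 to √1.16 = 1.08, so the same data give standard errors about 8% lower or higher according to row order. Average power at 0.678 SD is 0.841, against 0.850 for the two-sample test.

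**The case against.** The strongest reply is that the practical damage is small. Random pairing of independent women keeps the nominal type I error under the usual normality assumption and costs about one point of power. Any analyst who opened the data would see that there are no pairs and use a two-sample test. This is right about average error rates. It does not give the stated test a defined result: two analysts could follow the protocol and report different p-values, and unequal arms would force women to be dropped. An analyst who quietly substitutes another test has left the plan.

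Second, the protocol already plans a mixed-effects model of the quality-of-life trajectory. That model could carry the device contrast, and a model of this kind compares the devices on long-term acceptability. For quality of life, however, the text keeps the trajectory separate and gives cup versus cup+ to the paired test.

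Third, the primary outcome is six-hour leakage, which is untouched. That is true and limits the reach of the error, but quality of life is still one of the two targets used to size the trial.

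Fourth, perceived leakage is also collected at 6 h and 24 h in the clinic, where every woman uses both devices and pairing is legitimate. That stands: the error affects the monthly perceived-leakage data only.

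**Conclusion.** The concern holds. The protocol names a within-woman test for a between-woman comparison, and nothing elsewhere in the text supplies the missing pairs. This contradicts the stated design, so it is more than a detail left to the SAP. It must be corrected before the home-phase data are analysed.

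The conclusion about the test does not depend on any effect size. The consequence for power does. At about 80 retained women (1:1 assumed), the valid comparison detects 0.68 SD at 85% power, or 0.59 SD with baseline adjustment at an assumed r of 0.5. If the plan meant 0.40 SD, the only reading tried that yields 59, unadjusted power is 42% rather than 85%. If it meant 40 points with SD 28.1, 80 women are more than enough.

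**What to change.** 1. **Analysis section.** Replace the paired t-test for cup versus cup+ with one between-group analysis. A suitable choice is a mixed model for repeated measures on quality of life at months 1, 2 and 3, with randomised home device, visit, device-by-visit, baseline quality of life and site as fixed effects, and the month-3 device contrast as the result. ANCOVA at month 3 is a simpler alternative. The exact covariates are a choice; comparison between independent groups is not.
2. **Perceived leakage.** State that the monthly data use the same between-group approach. Table 2 shows no 0 h value for this measure, so say which clinic value, if any, serves as the covariate. Treat home adherence the same way if it is compared between devices.
3. **Paired tests.** Keep them for clinic-phase comparisons, such as short-term acceptability, where each woman uses both devices.
4. **Sample size.** State what the 40% refers to and its SD, recalculate for independent groups, and give the power expected with about 80 retained women.

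The cost is wording in the protocol and SAP, plus one recalculation. No new data or visits are needed. The article reports 16 women having completed the study, so the change could be made well before the final analysis. Only if the target really is 0.40 SD at 85% power does enrolment, or the claim made for this comparison, need to be reconsidered.

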### Study population and sample size

#### Quantitative

We will recruit up to 100 women with VVF to participate in the quantitative study activities (Aims 1–3). Study participation will not delay time to surgery for study participants through careful planning of recruitment efforts in alignment with timelines of surgical availability and through early study exit from community-based activities if surgery becomes available sooner. Our sample size calculation is not dependent on balance between study sites, thus the breakdown of participants by study site is not pre-defined but will depend on recruitment activities. Detailed inclusion and exclusion criteria are as follows:

*Inclusion criteria*: VVF confirmed by dye test and clinical exam at least three centimeters (cm) from the external urethral orifice regardless of size, adequate vaginal capacity to accommodate the cup (per physician), willing to insert and remove cup/cup+, clear understanding of the study procedures and willing to participate fully, not yet undergone surgical fistula repair or previously failed surgical repair, at least 6mo post-surgery if previous fistula repair, ≥3months post-delivery if recent birth, age 18 + or emancipated minor per Ghanaian or Kenyan law, and ability to speak English or local language.*Exclusion criteria*: Presence of any rectovaginal fistula (i.e., alone or in combination with VVF); not able to provide informed consent (e.g., incapacitated); does not leak more than 6 ml over 6 h during screening examination; and fistulas deemed curable via prolonged catheterization. Pregnant individuals will not be excluded from the study participation if they meet the inclusion criteria specified above. Pregnant or menstruating women will not be excluded and their experiences and outcomes will be compared to the larger sample.

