Cross-over trial designs provide greater efficiency than parallel designs due to within-subject treatment comparisons where each subject serves as their own control, resulting in lower sample size requirements for statistical power. Our sample size of up to 100 participants (400 observations) is calculated to assess: (1) a ≥ 65% reduction at six hours in observed urinary leakage, and (2) a mean 40% quality of life difference at three months between the cup and cup+ (measure range 0-100; Supplementary Figures). We expect > 80% retention over three months study follow-up based on our research with 12-months follow-up with 98% retention with this target population in Uganda^63^ and 3-months follow-up in Ghana with 84% retention, [64, 65] and have inflated our target sample size conservatively.

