Urine leaked (perceived) ^c^	Perceived difference in leakage (cup, cup+, leak free)^90,91^	PS		●	●		●	●	●
Acceptability (patient, family, clinician) ^c^	Ease, comfort, interference, likelihood to use or recommend	PS		●			●	●	●
	Barriers to use, concerns, use decision-making process	PS				●			

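### Adding each woman's clinic ratings of both devices to the long-term acceptability model could sharpen the home comparison of cup and cup+ at no data cost; this is an optional precision gain, not an error

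*Protocol article*

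**What the plan says.** Table 2, under Data collection, has one acceptability row, "Ease, comfort, interference, likelihood to use or recommend", marked at 6 hours in the clinic and again at 1, 2 and 3 months. Under the Quality of life analysis heading, short-term acceptability is "compared between cup vs. cup + using paired t-test (continuous") or McNemar's test for categorical measures. A paired test needs a rating of each device from each woman, which fits the crossover described under Randomization.

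The home phase comes afterwards and is parallel. Under Community-based procedures: "On the last clinic day, participants will be individually randomized to use of cup or cup + at home for up to three months".

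Long-term acceptability "will be described by cup vs. cup + through modeling their trajectory across community assessment", and the two devices are then compared by "comparing these statistically using mixed-effects linear regression analysis". The sentence lists no covariates and excludes none. The same section adds that secondary analyses will look at unspecified potential confounders for association with the acceptability score; clinic ratings are not named there.

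**The concern.** In the clinic each woman is her own control. At home she has one device, so the contrast between cup and cup+ is between women, and any stable difference in how women take to a vaginal device goes into the error term. The 6-hour clinic ratings use the same items and are collected before home use. They therefore serve as a baseline for the home outcome, and the stated model does not name them.

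Two other analyses in the article draw on more than the home visits. The leakage model is favoured because it uses everything collected, and the quality-of-life trajectory covers five assessment points. Acceptability is Aim 2, and the home phase is where sustained use is judged. At stake are the width of the interval for the long-term device contrast and protection against chance imbalance in prior attitude between two small arms.

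**Working it through.** **No planned figure to reproduce.** The sample-size section covers leakage and quality of life only. For acceptability the document gives no standard deviation, effect size or correlation. Every size below therefore rests on stated assumptions.

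**Number per home arm.** "We will recruit up to 100 women with VVF" gives at most 100 / 2 = 50 per arm if home allocation is 1:1 (the ratio is not stated). "We expect > 80% retention over three months study follow-up" gives about 0.80 × 50 = 40 per arm at three months.

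**Single home rating.** Let r be the correlation between the clinic covariate and the home rating. Adjustment multiplies the error variance by 1 − r², so a standardised effect d becomes d / √(1 − r²). Power is from the noncentral t, two-sided 5%, 40 per arm. An effect of d = 0.634 has 80% power unadjusted; d = 0.444 has 50%.

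| r (assumed) | Variance removed, r² | Power, from 80% | Power, from 50% |
|---|---|---|---|
| 0.1 | 1% | 80.4% | 50.4% |
| 0.2 | 4% | 81.6% | 51.6% |
| 0.3 | 9% | 83.6% | 53.8% |
| 0.4 | 16% | 86.4% | 57.1% |
| 0.5 | 25% | 89.9% | 61.9% |
| 0.6 | 36% | 93.8% | 68.8% |

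Charging two degrees of freedom changes these by less than 0.1 point. The gain passes 5 points only at about r = 0.4.

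**Mean of three home ratings.** This is closer to the planned repeated-measures model. If the home ratings correlate ρ with one another, the variance of their mean is σ²(1 + 2ρ)/3. A covariate correlated r with each of them reduces it to σ²[(1 + 2ρ)/3 − r²]. With ρ = 0.6 the starting factor is 2.2 / 3 = 0.733:

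- r = 0.1: 0.01 / 0.733 = 1% removed.
- r = 0.3: 0.09 / 0.733 = 12% removed.
- r = 0.5: 0.25 / 0.733 = 34% removed.

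For an assumed true difference of 0.4 SD, power at 40 per arm goes from 55% to 55%, 60% and 73%; at 50 per arm, from 65% to 65%, 70% and 82%. With r = 0.5, the share removed is 37.5% at ρ = 0.5 and 31% at ρ = 0.7.

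**Which clinic rating to use.** Suppose the model included only the clinic rating of the device the woman takes home. Its mean would differ between arms by the clinic device difference, Δc. With slope b on that covariate, the adjusted home contrast would be Δh − bΔc, which removes part of the device effect under study. If both ratings enter for every woman, each covariate has the same expected value in the two arms, because home allocation is random, and the contrast keeps its meaning.

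**The case against.** A reader might infer that the plan discards the clinic ratings. The text does not support that. The sentence fixes the outcome time points and the model family, and says nothing about covariates either way. Limiting the long-term outcome to home visits is right, and the fix keeps it. A covariate list may well sit in a statistical analysis plan that is not shown. This stands, and it is why the point concerns a stated model that could be improved rather than a mistake.

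A reader might also infer that the home comparison is biased or invalid. It is not: randomisation protects the unadjusted contrast. Nor does the article's preference for using all data in the leakage model create a contradiction, since that is a different outcome in a crossover analysis.

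The size is also open to challenge. The Background reports that 11 of 11 feasibility participants wore the cup comfortably and 10 of 11 would recommend it, which suggests a ceiling. It also says that acceptability may change over time and depends on context, and the Costing study section names distance to a latrine and access to water as influences on management at home. A 6-hour ward rating may predict home ratings poorly. Against this, insertion and removal were easy for only 8 of 11, so not every item was at its ceiling.

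Finally, the power table uses one home rating, whereas the planned model is repeated-measures and also keeps women with only earlier visits. Some acceptability measures may be categorical, and the 1 − r² formula does not carry over to them directly. The table therefore illustrates the mechanism; it does not forecast this trial's power.

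**Conclusion.** The point holds as an optional, low-cost improvement to the analysis of an outcome that is not primary; the article names 6-hour leakage change as the primary outcome variable. The stated long-term model does not include a baseline that the schedule already collects, and including it could narrow the home comparison.

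The size cannot be taken from the document. On a single home rating with 40 per arm, the gain from 80% power is at most about 2 points at correlation 0.1 to 0.2, about 4 points at 0.3 and about 10 points at 0.5. This assumes 1:1 home allocation, 80% retention, a roughly continuous score and clinic ratings made before home allocation. A claim that substantial precision is certainly being lost goes beyond the evidence, because the gain could be close to zero.

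**What to change.** In the analysis plan, keep the mixed model of the 1 to 3 month ratings and state that both clinic-phase ratings, of the cup and of the cup+, enter as covariates for every woman whichever device she takes home. For women in group 2, who have two cup periods under Randomization, use the average of the two cup ratings.

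Use only ratings recorded before home allocation. The 6-hour timing supports that order, but the text does not say so outright for the last clinic day, when the home randomisation takes place, so the plan should state it. Do not adjust only for the rating of the assigned device. If the unseen analysis plan already contains this adjustment, nothing further is needed.

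The cost is one sentence and about two degrees of freedom. No new data, visits or participants are required.
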